## TOPSY Protocol Version Log

| Version | Version Date                   | Significant Changes                                                                                                                                                                                                                                                                                                                                                                                                                                                                                                                                              |
|---------|--------------------------------|------------------------------------------------------------------------------------------------------------------------------------------------------------------------------------------------------------------------------------------------------------------------------------------------------------------------------------------------------------------------------------------------------------------------------------------------------------------------------------------------------------------------------------------------------------------|
| 1.0     | 29 th November 2017 | Protocol submitted to ethics for original application                                                                                                                                                                                                                                                                                                                                                                                                                                                                                                            |
| 2.0     | 08 th February 2018 | Protocol updated due to provisional opinion letter from ethics. This version of the protocol was used at the start of the pilot centre set up.                                                                                                                                                                                                                                                                                                                                                                                                                   |
| 3.0     | 27 th June 2018     | Minor clarifications in the protocol. Two clarifications on timings were added to the protocol so that centres were clear about acceptable timelines between screening and randomisation and randomisation and the teaching appointment. Randomisation should occur within 4 weeks of assessing eligibility (page 21)
The teaching appointment should take place within 4 weeks of the randomisation date (page 27).
The wording was changed slightly in consent pathway B on page 60. No processes were changed just a clarification |
| 4.0     | 17 th January 2019  | Update on the way centres can recruit women (additional phone call after clinical contact or after non response to postal pack) and outcome table on page 30.                                                                                                                                                                                                                                                                                                                                                                                                    |
| 5.0     | 25 th July 2019     | Clarifications on timings and Section 9.9                                                                                                                                                                                                                                                                                                                                                                                                                                                                                                                        |
| 6.0     | 22 nd July 2020     | An additional questionnaire to capture the impact of COVID-19 on participants' views on pessary care/ self-management. Addition of COVID 19 protocol annex                                                                                                                                                                                                                                                                                                                                                                                                       |
| 7.0     | 23 rd November 2020 | Updated project timelines for 6 month extension                                                                                                                                                                                                                                                                                                                                                                                                                                                                                                                  |
| 8.0     | 11 h March 2022     | Addition of Appendix D, protocol Annex for 4 year follow up                                                                                                                                                                                                                                                                                                                                                                                                                                                                                                      |
| 9.0     | 18 TH May 2022      | Change of Sponsor                                                                                                                                                                                                                                                                                                                                                                                                                                                                                                                                                |
| 10.0    | 02 nd August 2022   | Update on funder contact details (P57/58); addition of SWAT 86 to Appendix D (Participant Selection and Enrolment); update on adverse and serious adverse event report to Appendix D; and addition of Appendix E (SWAT 86 Protocol)                                                                                                                                                                                                                                                                                                                              |
| 11.0    | 08 th November 2022 | Addition of Appendix F, protocol annex for APPLE (sub-study of TOPSY)                                                                                                                                                                                                                                                                                                                                                                                                                                                                                            |

## PROTOCOL SUMMARY TABLE

|                            |                                                                                                                                                                                                                                                                                                                                                                                                                                                                                                                                                                                                                                                        |
|----------------------------|--------------------------------------------------------------------------------------------------------------------------------------------------------------------------------------------------------------------------------------------------------------------------------------------------------------------------------------------------------------------------------------------------------------------------------------------------------------------------------------------------------------------------------------------------------------------------------------------------------------------------------------------------------|
| QUESTIONS ADDRESSED | 
 
1. What is the clinical and cost-effectiveness of self-management of vaginal pessaries to treat pelvic organ prolapse, compared to standard pessary care, on condition-specific quality of life?
 
2. What are the barriers and facilitators to intervention acceptability, intervention effectiveness, fidelity to delivery, and adherence for women treated with vaginal pessary and the healthcare professionals who treat them, and how does this differ between randomised groups?
 
                                                                                                       |
| TRIAL PARTICIPANTS  | Woman 18 years or older with prolapse of any type or severity, who have successfully used a pessary for at least two weeks.                                                                                                                                                                                                                                                                                                                                                                                                                                                                                                                            |
| TRIAL ENTRY         | Consent will be obtained from eligible women after written and verbal information has been provided.                                                                                                                                                                                                                                                                                                                                                                                                                                                                                                                                                   |
| INTERVENTIONS       | 
 
1. Women in the standard care group will be seen at regular intervals (as per local centre protocol) to have their pessary removed and a new one inserted.
 
2. Women in the self-management group will have a 30 minute teaching appointment with a healthcare professional trained in delivery of the self-management intervention who will teach women to remove, clean and re-insert their pessary. Women will receive a follow up phone call and a phone number to call if problems are experienced.
 
                                                                                     |
| OUTCOMES            | 
Primary outcome measure is prolapse-specific quality of life (PFIQ-7).
 
Secondary outcomes/Questionnaires;
 
 
• Generic quality of life (EQ-5D-5L)
 
• Prolapse symptoms (PFDI-20);
 
• Sexual dysfunction (PISQ-IR);
 
• Self-efficacy (GSE)
 
• Pessary Use Questionnaire (Patterns of pessary use, acceptability and benefit)
 
• Pessary complications
 
• Pessary Confidence Questionnaire (Efficacy)
 
• Adherence to trial group; crossover to other group.
 
• Resource Use Questionnaire (for health economic evaluation)
 
 |
| CO-ORDINATION       | 
Local: by local lead Principal Investigator, an Intervention healthcare professional and a Recruitment Officer.
 
Central: by TOPSY Study Glasgow Office in Glasgow Caledonian University.
 
Overall: by the Project Management Group and overseen by the Trial Steering Committee and the Data Monitoring and Ethics Committee.
                                                                                                                                                                                                                                                                                                      |

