## **4. STUDY POPULATION**

### **4.1 Sample Size Calculation**

A sample size of 330 women (165 per group) is required to provide 90% power to detect a difference of 20 points in the PFIQ-7 score at 18 months, assuming a standard deviation of 50, two-sided alpha of 0.05, and 20% loss to follow-up. In order to detect this standardised effect size of 0.4 SDs (20/50 points), 132 women will need to be recruited per group, or 165 per group to allow for dropout. Since the identified centres each see approximately 35 women a month for pessary care, we aim to recruit two to three women per month per centre.

The aim is to recruit a sample size sufficient to detect a 20-point difference in the PFIQ-7 score (the potential range of the PFIQ-7 is 0 to 300), although we acknowledge that an appropriate minimum clinically important difference for PFIQ-7 has not been formally determined. Barber et al. (2005) suggested a minimum clinically important difference (MCID) of 36 points, but it was emphasised that this was based on a small sample and applies only to within-group rather than between-group differences. Therefore, as part of the internal pilot, we will canvass PPI, investigators, and other participating clinicians to gauge the perceived importance of a 20-point difference.

Two recent trials which have used PFIQ-7 in populations of women using pessaries have reported SDs at 12 months and 24 months between 25 and 40 (Weigersma et al., 2014; Panman et al., 2016). These studies however were relatively small, conducted in only a few centres, and neither measured PFIQ-7 at 18 months. Given this uncertainty, a conservative assumption that the SD may be as high as 50 has been made. This will be monitored by examining the variability in the PFIQ-7 score for those women recruited in the internal pilot and we will continue to monitor the aggregated (blinded) SD regularly (every 40 cases using six-month outcome data; and as cases complete at 18 months), with a view to re-estimating the sample size at an appropriate point if required.

A sample size of 330 also provides power for the analysis of secondary outcomes, e.g. we will have more than 90% power (2-sided 5% level of significance) to detect a 20% difference in pessary use continuation rate (assuming at least 50% in the standard care group continue to use a pessary at 18 months).

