## 8 PROPOSED ANALYSES

### 8.1 Quantitative data analysis

All analyses will be conducted according to a pre-specified statistical analysis plan. All outcomes will be described with the appropriate descriptive statistics where relevant: mean and SD for continuous outcomes (or medians and interquartile range for skewed data), and counts and percentages for dichotomous and categorical outcomes.

The main effectiveness analysis will be based on the ITT principle. The analysis of the primary outcome will estimate the mean difference (with 95% confidence intervals) in the PFIQ-7 score at 18 months between the self-management and standard care groups using a mixed effects repeated measures model (which assumes incomplete outcome data to be missing at random). The model will incorporate PFIQ-7 scores at baseline, 6, 12 and 18 months, with age (<65/≥ 65) and pessary user type (new/existing) as fixed effects and recruitment centre as a random effect. Missing baseline data will be imputed. The repeated measures model will also estimate mean differences in PFIQ-7 at six and 12 months. Statistical significance will be at the 5% level.

The missing at random assumption for primary outcome data will be assessed further in sensitivity analyses. Treatment effects will be estimated under varying assumptions of data being missing not at random using pattern-mixture models. A complete case analysis will also be conducted.

Secondary outcomes will be analysed using an appropriate generalised linear model (for example binary logistic regression for dichotomous outcomes such as discontinuation with pessary (Y/N), and ordinal logistic regression for ordered categorical outcomes such as women's global impression of improvement (PGI-I). All models will be adjusted for minimisation covariates (age, pessary user type and centre) and baseline score (where applicable).

Given the potential for crossover, we will conduct a secondary analysis of compliers to estimate the effect of receiving the self-management intervention, using complier average causal effect (CACE) estimators. The CACE analysis will take a maximum likelihood approach, which can assume incomplete data to be missing at random, and can be adjusted for covariates. This analysis will provide unbiased effect estimates of receiving the self-management intervention, which will complement the unbiased ITT effect estimates of being offered self-management.

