#### ***Intervention Healthcare Professional (HCP)***

Each collaborating centre will appoint a local Intervention HCP as part of the local TOPSY research team who will be trained on the self-management intervention and who will keep regular contact with the local PI, with notification of any problem or unexpected development.

Each centre will have a centre initiation visit to ensure all study processes are in place before recruitment commences. The TOPSY Study Glasgow Office will set-up regular centre 'forums' for all centres to 'phone in' and discuss any problems experienced and share learning. Updates will be provided via quarterly newsletters. Centres having specific problems with recruitment and/or retention will be offered additional support either remotely or by an additional centre visit.

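### If intervention HCPs differ in how well they teach self-management, the primary model's centre intercept leaves that variation out of the standard error, and no sensitivity analysis for it is stated

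*Protocol*

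**What the plan says.** The summary table describes local co-ordination as being "by local lead Principal Investigator, an Intervention healthcare professional and a Recruitment Officer", and the intervention as a "30 minute teaching appointment with a healthcare professional trained in delivery of the self-management intervention". Section 9.4 adds: "Each collaborating centre will appoint a local Intervention HCP as part of the local TOPSY research team". Under section 6.1, an HCP trained for the trial teaches each woman one-to-one, the HCP who treated her makes the two-week call, and later problems go to the intervention HCP at her centre. Section 7.1.3 (adherence) says the trial's teaching and support are closed to standard-care women.

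For the primary outcome, section 8.1 fixes a mixed repeated measures model with age group and pessary user type "as fixed effects and recruitment centre as a random effect". It names no HCP term and no centre-by-treatment term. The sensitivity analyses that it lists for the primary outcome deal with missing data, and the complier analysis deals with crossover.

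Section 4.1 states that "A sample size of 330 women (165 per group) is required to provide 90% power", "assuming a standard deviation of 50, two-sided alpha of 0.05, and 20% loss to follow-up", and that "132 women will need to be recruited per group, or 165 per group to allow for dropout". It makes no allowance for clustering.

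**The concern.** Women taught by the same HCP share whatever is specific to that HCP's teaching. This sharing exists in the self-management arm only, so the design is partially nested.

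A centre random intercept does not deal with it. Women are randomised within centre, with centre as a minimisation factor, so a centre's intercept enters both arms and largely cancels from the treatment difference. Variation between HCPs in the effect of teaching behaves like a treatment effect that varies from centre to centre, and an intercept cannot carry that into the standard error.

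The protocol gives reason to expect some variation. Section 6.1 allows nurses, physiotherapists, urogynaecologists or GPs to deliver the intervention, and section 7.2 sets out to ask staff about differences in delivery. That enquiry feeds the process evaluation, not the trial estimate. The result is meant to inform NHS practice beyond the staff who took part, so the interval would be somewhat too narrow for that use if HCPs differ.

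**Working it through.** **Inputs from the protocol.** Difference 20, SD 50, two-sided alpha 0.05, 132 evaluable per arm (section 4.1). Centres: 17 planned (section 4.4), 21 reported in Appendix C.

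**Inputs assumed.** HCP ICC (ρ) of 0.02 to 0.05, with 0 and 0.01 for comparison. One HCP per centre, which is the least favourable reading of the staffing.

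**Step 1: reproduce the plan.** The normal-approximation formula gives 132 per arm, and 132/0.8 = 165. The standard error is 50 × √(2/132) = 6.155, and power is Φ(20/6.155 − 1.96) = 90.1%. The stated figures are right for independent women.

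**Step 2: add HCP clustering in one arm.** With m self-management women per HCP,

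Var = SD²/n + SD²[1 + (m − 1)ρ]/n.

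The ratio of true to nominal standard error is r = √{(1 + [1 + (m − 1)ρ])/2}. Type I error is 2[1 − Φ(1.96/r)], and power is Φ(20/(6.155r) − 1.96).

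Example with 17 centres and ρ = 0.05: m = 132/17 = 7.76; design effect 1 + 6.76 × 0.05 = 1.338; r = √(2.338/2) = 1.081; standard error 6.65.

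| Centres | m | ρ | r | Type I error | Power | Total N for 90% with 20% loss |
|---|---|---|---|---|---|---|
| 17 | 7.8 | 0.01 | 1.017 | 5.4% | 89.2% | 342 |
| 17 | 7.8 | 0.02 | 1.033 | 5.8% | 88.2% | 354 |
| 17 | 7.8 | 0.05 | 1.081 | 7.0% | 85.2% | 386 |
| 21 | 6.3 | 0.01 | 1.013 | 5.3% | 89.4% | 340 |
| 21 | 6.3 | 0.02 | 1.026 | 5.6% | 88.6% | 348 |
| 21 | 6.3 | 0.05 | 1.064 | 6.6% | 86.3% | 374 |

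At ρ = 0, r = 1 and nothing is lost. If centre sizes vary with an assumed coefficient of variation of 0.6, r is 1.037 to 1.113 for ρ of 0.02 to 0.05, and power is 83 to 88%.

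**Step 3: check that the centre intercept does not absorb it.** Null trials of 264 women were simulated (3,000 per setting, unequal centres, assumed centre ICC 0.03) and analysed with a centre random intercept only, by REML with a z-test. With 17 centres and ρ = 0.05, the model's mean standard error was 6.01 against a true SD of the estimate of 6.88, and 8.9% of trials rejected. With 21 centres the rejection rate was 7.1%. At ρ = 0 the rates were 5.5% and 5.4%, so a little of the excess over 5% is not due to HCPs.

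**Step 4: two HCPs per centre.** The women per HCP halve. Then r is 1.01 to 1.04 and type I error is 5.3 to 5.8% for ρ of 0.02 to 0.05 (equal sizes): same direction, smaller.

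**The case against.** *The staffing.* A reader might infer that one HCP teaches every self-management woman at a centre. The protocol does not guarantee that. The lines in the summary table and section 9.4 can be read as naming a role. Section 6.1 speaks of those delivering self-management at a centre in the plural, and section 7.2 asks to interview at least one deliverer per centre. Six to eight women per HCP is therefore an upper reading. This stands, and it reduces the size.

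*The comparator.* A reader might also infer that standard care has no provider effect. It does: section 6.2 has it delivered by professionals at each centre, and sections 5.1.1 and 5.1.7 allow the same staff to deliver both. Any quality common to both arms is already in the centre intercept. Only the part specific to self-management teaching is missed, and the manual, training and leaflet will restrain it.

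*The power.* SD 50 is deliberately conservative, since section 4.1 cites 25 to 40 from other trials and plans blinded SD monitoring. At SD 40, power with 132 per arm is 98%, and still about 95% at r = 1.113. So the trial is not shown to be underpowered. What stands is that the stated 90% at SD 50 rests on an unstated assumption.

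*The remedy.* Putting a centre-by-arm term with small-sample degrees of freedom into the primary model has a price. In a simulation with balanced centres and no true HCP variation, the variance was estimated above zero in about 46% of trials. Intervals were 9 to 10% wider on average, power fell by about 4 points, and type I error dropped to about 3.6%. That argues against replacing the primary model, but not against a sensitivity analysis.

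*The SAP.* Section 8.1 defers to a separate SAP, which is not at hand and may contain such an analysis. The protocol nevertheless fixes the model's grouping structure and states its own sensitivity analyses, and neither addresses HCPs.

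**Conclusion.** The point holds conditionally. The protocol establishes that HCP teaching and support occur in one arm only, and that the primary model's only grouping term for it is a centre intercept. If HCPs differ in the effect of their teaching, the standard error of the treatment difference is too small.

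Under one HCP per centre, 17 to 21 centres of equal size and an assumed ICC of 0.02 to 0.05, the understatement is about 3 to 8%, type I error is about 5.5 to 7%, and power at SD 50 is about 85 to 89%. It is somewhat worse with unequal centres, smaller with several HCPs per centre, and nil at an ICC of 0. The power figures take no credit for baseline adjustment.

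A reader might conclude that the planned interval and p-value are simply wrong. The protocol does not support that, because it gives no ICC and no evidence that HCPs actually differ in effect.

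**What to change.** Keep the stated primary model. In section 8.1, and in the Appendix D plan for the 4-year analysis, pre-specify one sensitivity analysis of the primary outcome. It should add a random intervention-HCP effect in the self-management arm, or a random centre-by-arm term, use small-sample degrees of freedom, and be reported beside the primary result. In section 4.1, say that 90% assumes no HCP clustering and give the power for an assumed ICC of 0.02 to 0.05.

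On timing, section 9.6 had the 18-month analysis complete by January 2022. A change to this version (November 2022) is therefore prospective only for the 4-year analysis, scheduled for November 2023 to January 2024. For the 18-month result it should be labelled as an added analysis unless the SAP already contains it.

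The cost is a little more analysis and a slightly less favourable stated power. The HCP version needs an identifier for each woman's teacher; Table 7.2 already has staff complete a CRF for each teaching appointment, so this should be confirmed there. The centre-by-arm version needs no new data.
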